### 2.4. Data Processing

#### 2.4.1. Whole-Body Movement and Coordination Testing

Trajectories will be examined using Visual 3D (v6, C-Motion Inc., Germantown, TN, USA) after markers have been labeled. Using residual analysis, raw marker coordinates will be low-pass-filtered (4th-order Butterworth) with cut-off frequencies of 12 Hz and 8 Hz. Joint angle data for flexion-extension, internal-external rotation, and abduction-adduction (x-axis, z-axis, and y-axis, respectively) will be determined as the transformation between two segment coordinate systems (SCSs) given by an X-Y-Z Cardan sequence of rotations. Extension/plantarflexion and flexion/dorsiflexion will be represented by positive and negative angles, respectively. A variant of Ridder’s split difference method will be used to differentiate linear and angular values [83]. Newton-Euler inverse dynamics algorithms will be used to calculate the generated joint moments. The product of joint power will then be determined.

Movement task (i.e., throwing): Joint angular kinematics, kinetics, coordination, and coordination variability will be assessed. Movement coordination will be captured using vector coding and principal component analysis. Characteristics of a candidate collective variable for throwing will also be included in the analysis, described by the phase relation between the total body mass center of wrist location. The analysis of balance (mBESS stance), dynamic balance (tandem gait), and coordination (finger-to-nose task) are based on published clinical measures.

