### 2.2. Measures and Experimental Procedure

#### 2.2.1. Demographics

Age, gender, training duration, medical history, the use of medication, (e.g., mental health issues), health habits (e.g., activity prior to blood draw, alcohol consumption, smoking), rugby playing history, position, and history of concussion will all be recorded at the outset. Personalized anthropometric measures, as well as stature and total body mass, will be recorded for each player using digitized coordinate data from whole-body static pictures. Body segment inertia properties, such as segment masses, moment of inertia, and total body mass center position, will be provided by these measures; the methods described in Gittoes et al., 2009, and Yeadon, 1990 [70,71], will be employed.

The measures and experimental procedures for (2) blood and (3) biomechanical and cognitive-motor tasks and (4) notational analysis are presented below in Section 2.2.2 and Section 2.2.3. The analysis of the data will be combined to address the specific multivariate nature of the research questions.

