### 2.3. Experimental Procedure

#### 2.3.1. Whole-Body Movement and Coordination Testing

Four whole-body tasks will be completed within the motion capture area: an ecologically valid movement task (i. throwing task), (ii. tackle task), balance (iii. mBESS stance), dynamic balance (iv. tandem gait), and coordination (v. finger-to-nose task).

Throwing task: During the validated movement task, participants will undertake expected and unexpected passing practices in which they will run and pass at top speed to a target (Figure 2). During the anticipated pass, the player will start at a standstill and then will run forward 5 m at full pace to a performing zone, where they will throw a rugby-style pass to the left and right to a target 6 m away; this will be performed 3 times (3-left; 3-right). In the unanticipated task, a light (SMARTSPEED pro, Fusion sport, Australia) in front of the participant will indicate the direction of the pass in a pseudo-random order when they reach 0.5 m from the target line. A successful pass will be one that hits the target, as shown in Figure 2 and as evaluated by a National Performance Director. Data collection: during the whole-body movement and coordination tasks, participants will be labeled using a modified full-body 6-DOF kinematic model [72,73]; using double-sided tape, 38 retroreflective markers (14 mm in diameter) will be applied to the skin (Figure 3). Three-dimensional kinematic (14 cameras, Vicon Vantage Oxford Metrics, Oxford, UK, 250 Hz) and kinetic data will be obtained (force plates: four 600 mm × 900 mm Kistler 9287BA, Winterhur, Switzerland). All cameras will be calibrated to residual errors of <0.3 mm using a 240 mm calibration wand. Prior to further analysis, the external force signals will be amplified internally and aggregated with kinematic data using Vicon Nexus (v2.2.3) and filtered using a low-pass method (4th-order Butterworth, 60 Hz cut-off). Body segment inertia parameters will be based on work by De Leva (1996), as successfully used across a number of dynamic sporting movements [72,73,74].

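### Throwing-task joint moments and powers combine force filtered at 60 Hz with markers filtered at 12 and 8 Hz, leaving an impact remainder; separately, two sources of segment inertia are named and not reconciled

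*Protocol article*

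**What the plan says.** All references are to the Protocol article.

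**Filtering.** Section 2.3.1 says the external force signals are "filtered using a low-pass method (4th-order Butterworth, 60 Hz cut-off". Section 2.4.1 says "raw marker coordinates will be low-pass-filtered (4th-order Butterworth) with cut-off frequencies of 12 Hz and 8 Hz". It does not say which of the two marker values applies to which task, marker or axis.

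**Use.** Section 2.4.1 continues: "Newton-Euler inverse dynamics algorithms will be used to calculate the generated joint moments", then "The product of joint power will then be determined". For the throw, "Joint angular kinematics, kinetics, coordination, and coordination variability will be assessed". In section 2.3.1 the player in the anticipated pass "will run forward 5 m at full pace to a performing zone" before passing, with force plates recording. The Introduction names changes in joint moments and power as something the synchronised plates should show.

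**Segment inertia.** Section 2.2.1, after describing personalised measurements digitised from photographs of each player, says: "Body segment inertia properties, such as segment masses, moment of inertia, and total body mass center position, will be provided by these measures". Section 2.3.1 says "Body segment inertia parameters will be based on work by" a different published source, dated 1996. Neither section refers to the other.

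**The concern.** Inverse dynamics obtains joint loads by setting the measured ground force against segment mass times acceleration, with the acceleration taken from the markers. The two sides must carry the same frequency content. If a foot-strike transient passes through the force filter but is largely removed by the marker filter, the calculation assigns the difference to the joint, first as a moment and then as power.

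A constant artefact would tend to cancel in a change from baseline. This one scales with how hard the foot lands. The first hypothesis in the Introduction expects whole-body movement to decline over the games. If players also ran in more slowly, the artefact would shrink and could pass for a change in technique. Section 2.5 applies statistical parameter mapping to continuous data. If joint-moment curves are included, an early-stance artefact could show as a localised difference.

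The inertia conflict is a different matter. The same Newton-Euler model has two stated sets of inputs, so the method is not defined.

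**Working it through.** The article gives no figure for this effect, so there is none to reproduce. The check has four steps.

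**Inputs from the article:** force cut-off 60 Hz (section 2.3.1); marker cut-offs 12 and 8 Hz (section 2.4.1); Butterworth filters, 4th order. **Assumed, because not in the article:** impact pulse shape and duration; zero-lag filtering; and, for step 3 only, segment mass, joint force and touchdown speed.

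**Step 1. Filter gain at 20 Hz.** The gain at frequency f with cut-off c is 1/√(1+(f/c)^8) for a single-pass 4th-order filter and 1/(1+(f/c)^4) for a 2nd-order filter run forward and back.

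- 60 Hz: (20/60)^4 = 0.012, gain 0.99 (single pass 1.00)
- 12 Hz: (20/12)^4 = 7.72, gain 1/8.72 = 0.115 (single pass 0.129)
- 8 Hz: (20/8)^4 = 39.1, gain 1/40.1 = 0.025 (single pass 0.026)

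If the cut-off is corrected for the two passes (divided by 0.802), the two-pass gains at 20 Hz become 0.99, 0.24 and 0.06. That is milder, but the pattern is the same.

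**Step 2. Half-sine pulse through the zero-lag filter with corrected cut-off.** The remainder is the largest pointwise difference between the pulse filtered at 60 Hz and at the marker cut-off, as a fraction of the unfiltered peak.

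| Pulse | Peak kept at 8 / 12 / 60 Hz | Remainder, 60 v 12 Hz | Remainder, 60 v 8 Hz |
|---|---|---|---|
| 20 ms | 0.27 / 0.40 / 0.98 | 0.58 | 0.71 |
| 30 ms | 0.40 / 0.56 / 1.00 | 0.44 | 0.60 |
| 50 ms | 0.60 / 0.78 / 1.00 | 0.22 | 0.40 |
| 100 ms | 0.89 / 0.98 / 1.00 | 0.11 | 0.19 |

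At 20 ms and 8 Hz the remainder is 0.98 − 0.27 = 0.71. At 50 ms and 12 Hz the difference in peaks is 1.00 − 0.78 = 0.22 (0.23 pointwise). At 100 ms the peak kept at 12 Hz suggests a loss of only 2%, but the two curves differ most away from the peak, by about 11%.

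**Step 3. One-segment illustration.** Joint force = m·a − F, with m = 5 kg, a smooth joint force peaking at 1800 N, a sine-squared impact pulse and vertical touchdown speed from 0.8 to 2.5 m/s. The result is the largest joint-force error in the first 60 ms of contact.

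| Force / marker cut-off | 30 ms pulse | 50 ms pulse |
|---|---|---|
| 60 / 12 Hz | 141 to 442 N | 53 to 167 N |
| 60 / 8 Hz | 177 to 554 N | 81 to 252 N |
| 12 / 12 Hz | 25 to 33 N | 18 to 21 N |
| 8 / 8 Hz | 72 to 74 N | 68 to 70 N |

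With unequal cut-offs the error is proportional to touchdown speed: 442/141 = 3.1 and 2.5/0.8 = 3.1. With a common cut-off of 12 or 8 Hz it is nearly flat. A common 8 Hz is not always the smaller error (about 70 N against 53 N for 60/12 Hz at 50 ms and the lowest speed), because heavy smoothing also blunts the true joint force. What it removes is the dependence on speed.

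**Step 4. Inertia sources side by side.** Section 2.2.1 has segment masses and moments of inertia measured for each player from images. Section 2.3.1 bases the parameters on a published 1996 source. Table 1 lists body segment inertia among the baseline measures, so under section 2.3.1 as written a collected measurement may go unused.

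**The case against.** **Size.** The remainder in step 2 is a share of one segment's inertial peak, and a reader might infer a joint-moment error of that size. The documents do not support this. In step 3 the error is about 8-31% of the assumed 1800 N peak (141/1800 to 554/1800) for a 30 ms pulse and 3-14% (53/1800 to 252/1800) for 50 ms, and these figures move with the assumed mass and speed. This objection stands.

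**Importance.** One might call joint kinetics a headline outcome. They are a named outcome. The sample size rests on blood biomarkers (section 2.1), and the Discussion's stated movement expectations concern balance, finger-to-nose, passing accuracy and coordination variability. The effect is confined to ground-contact kinetics in the throw. This stands.

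**Bias.** A reader might conclude that sessions or groups are biased. The instruction is maximal speed every time, and nothing says approach speed will fall. If it did, true joint moments could change too, so speed would confound the comparison under any filter. Between-group bias is possible but not shown. This stands.

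**Inertia.** It is tempting to count the inertia conflict as a second cause of the artefact. It is not. Either source, used consistently, applies to a player at every session and largely cancels in change from baseline. The contradiction remains.

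**Condensed text.** Choosing cut-offs by residual analysis and then stating two values is not contradictory, and where each applies may be set out in a fuller protocol. The forces might also be refiltered later. But the article states both force and marker settings, and then a calculation that uses both, without saying so. That part of the objection does not remove the point.

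**Conclusion.** Two separate points hold.

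First, followed as written, the settings leave an impact remainder in the early-contact joint moments and power of the throw: 44-71%, 22-40% and 11-19% of the segment inertial peak for pulses of 20-30, 50 and 100 ms. These figures rest on a half-sine pulse and a zero-lag filter. The resulting joint-moment error cannot be stated from the article. The remainder grows with impact speed. Linking this to approach speed assumes that the two rise together, and distortion between sessions requires that approach speed actually changes. Joint angles, coordination, balance, cognitive and blood outcomes are not affected.

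Second, sections 2.2.1 and 2.3.1 give incompatible sources for segment inertia. This needs no assumption.

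Both should be corrected before processing starts. Neither touches the sample size or the biomarker comparison.

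**What to change.** - For inverse dynamics only, filter force and marker data at one common cut-off, chosen by residual analysis and held constant across players and sessions. Keep the 60 Hz force signal for variables that use force alone.
- In section 2.4.1, say where 12 Hz and 8 Hz apply if both are kept for kinematics.
- Name one inertia source in both sections 2.2.1 and 2.3.1. The personalised measures are already collected at baseline.
- Report approach speed, computed from the marker data, alongside the kinetic outcomes.

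The cost is processing settings and a few sentences; no new data are collected. The small downside is that impact peaks in the joint moments will be smoother and lower, since matching also removes real impact content from the force.

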#### 2.4.2. Cognitive-Motor Tasks

The cognitive-motor tasks will be examined using the standard clinical procedure. Specifically, Stroop word test: Scores will be reported as the average response time in incompatible trials minus compatible trials. Reaction time task: The task will be scored digitally in milliseconds. Purdue Pegboard: The number of pins inserted in the time period for each hand determines the score for the pin (peg) insertion subtests. The total number of pairs of pins inserted determines the score for the bimanual condition. The assembly score is the number of components assembled (for more information on how to set up/run a test, check the extended usage instructions in the Scoring Application or on our website). Finally, Tapping Task: Timing, consistency, and frequency will be quantified.

### 2.5. Statistical Analysis

Data will be analyzed using IBM SPSS 26.0. Diagnostic testing (e.g., outlier detection, distribution examination, homogeneity checking) will be conducted for all data, and all skewed values and missing values will be addressed using a multiple imputation approach. To examine the differences between the baseline and the testing days for each of the physiological, cognitive-motor, and whole-body movement skills, a series of generalized linear mixed models will be employed, controlling for several demographic covariates. Post hoc tests will be performed using the Bonferroni procedure, Mann-Whitney U test, and Chi-square test for different types of data. The significance level will be set at 95% (two-tailed). The effect size of Cohen’s d will be calculated, with 0.3, 0.5, and 0.8 indicating small, medium, and large effect sizes, respectively.

Due to the difference in the type of data (discrete and continuous), a variety of methods will be employed, including statistical parameter mapping to examine continuous data between the four sessions and baseline. A canonical analysis will be used as a multivariate technique to determine the relationships between the variables and the selected performance of key dependent variables. All collected data will be anonymized and stored on a password-protected computer, with access only granted to the lead investigator.

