In order to understand the facets of motor control function that may underpin changes in the performance of gross motor skills, it is important to perform a number of tests of executive function and specific aspects of perception-action coupling. For example, reaction time is a promising indicator of visuo-motor deficits following SRC [65], which is quick and easy to quantify. Finger-tapping and fine motor skill tasks (f/e the Perdue Pegboard test) [66,67,68,69] have been used widely in cognitive psychology to identify neurological conditions. In order to understand the facets of motor control function that may underpin changes in the performance of gross motor skills, we will perform a number of perception-action and physical tasks. Specifically, we will explore reaction time, executive function (Stroop word test), and fine motor skills (finger tapping and Perdue Pegboard).

The study’s aim, therefore, is (1) to examine changes in biomarker concentrations and biomechanical and cognitive-motor abilities of elite rugby players across three-match tournaments until 72 h after the final game and (2) to explore the relationship between subconcussive head impacts and their intensity and changes in blood biomarker concentrations, biomechanical tasks, and cognitive-motor tasks.

It is hypothesized that (1) the whole-body movement, coordination, and cognitive-motor tasks will decrease significantly with the duration of games played because of fatigue and/or concussive events; (2) blood biomarkers (i.e., CK, cardiac troponin T, NSE, S100B, BDNF, GFAP, and UCHL1) will increase significantly after rugby tournaments; (3) a correlation will be explored between the number of head impacts (quantified with a notational analysis) and the aforementioned indicators. The study has been registered as a clinical trial (clinicaltrials.gov NCT04841876 (assessed on 16 March 2022)) and has been approved by the Research Ethics Committee of Hong Kong Baptist University (REC/20-21/0452).

All data collection, including motor control, biomechanics, and blood analyses, will be performed through formal collaboration with the universities constituting the Sport and Health Interdisciplinary Group in Movement & Performance from Acute & Chronic Head Trauma (IMPACT) research group based at Cardiff Metropolitan University. Funding for this project will be covered by the institutes involved.

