## 2. Materials and Methods

### 2.1. Study Design and Participant Recruitment

This study will be a randomized control trial. The study will consist of two groups: one sport-event group (SG) and one control group (CG); see Figure 1.

Sample sizes were calculated using G*Power 3.1 software (Heinrich-Heine-University Dusseldorf, Dusseldorf, Germany). Calculations were based on a previous study [7], and we aimed to achieve a substantial effect size of 0.8 (Cohen’s d) on blood biomarkers. With an alpha of 0.05 and a power of 80%, 40 participants (20 participants per group) are required to achieve a robust estimation of the relevant parameters. All participants will be required to be over 18 years of age to participate in the study. Prior to data collection, all participants will be fully familiarized with testing procedures and the laboratory environment. In addition, a pilot study will be performed prior to actual experimental data collection. This will provide valuable information concerning timing, standardization, subject preparation, data collection information, logistics, and experimental organization in terms of data management for all participants pre- and post-testing. Members of the research team supervising each different aspect of data collection will ensure the standardization and integrity of data collection. Blood samples will be collected at several phlebotomy locations to ensure bloodletting is performed immediately post-match. There will also be several locations provided by the research team to collect biomechanical and cognitive-motor task data. These multiple locations will enable efficiency and effectiveness in data collection post-event, minimizing the effect of time as a confounding variable.

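### Section 2.5 puts observed skewed values under multiple imputation; applied as written, this replaces genuine high biomarker readings and biases the sport–control difference toward zero by an amount the article does not fix

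*Protocol article*

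**What the plan says.** Section 2.5 of the protocol article first sets out the screening step: "Diagnostic testing (e.g., outlier detection, distribution examination, homogeneity checking) will be conducted for all data". The same sentence then says that "all skewed values and missing values will be addressed using a multiple imputation approach". One method thus covers two classes of value, one observed and one not. The section gives no definition of a skewed value, no cut-off, no transformation and no exemption for verified readings, and nothing elsewhere in the article narrows the sentence.

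The main analysis follows: "a series of generalized linear mixed models will be employed, controlling for several demographic covariates".

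The Introduction states the expected direction, that "blood biomarkers (i.e., CK, cardiac troponin T, NSE, S100B, BDNF, GFAP, and UCHL1) will increase significantly after rugby tournaments", and the second aim, "to explore the relationship between subconcussive head impacts and their intensity and changes in blood biomarker concentrations". The Discussion (Section 3) repeats that these markers are expected to rise after a match. Section 2.1 ties the sample size to the same outcomes: "we aimed to achieve a substantial effect size of 0.8 (Cohen’s d) on blood biomarkers".

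**The concern.** Skewness describes a distribution. It is not a fault in a single measurement, and imputation cannot act on a value until that value has been removed. Read plainly, the sentence tells the analyst to flag observed readings during diagnostics, blank them, and redraw them from a model fitted to the readings that were not flagged.

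In this trial that selection depends on the outcome. If matches raise the markers, and heavier impacts raise them more, the upper tail after matches is where the effect lies, and most of that tail belongs to the sport group. Redrawing it from the unflagged values lowers the sport-group mean more than the control mean. At stake are the test of the biomarker hypothesis, in the direction of a false null, and the exploratory relation between head impacts and biomarker change. Because the term is undefined, the choice of readings to replace would also be made after the data are seen.

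This is a stated rule, not a detail left to an analysis plan. A plan that followed it would carry the error forward.

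**Working it through.** The article gives no figure for this rule, so there is none to reproduce. The check has two parts: direction by algebra, and size by simulation under stated assumptions.

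**Direction.** Let f be the share of a group's values that are flagged, and δ the mean amount by which flagged values exceed their imputed replacements. Each group mean falls by f × δ, so

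D(after) = D(before) − f(sport) × δ(sport) + f(control) × δ(control).

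If high values are flagged, and flagged more often or more heavily in the sport group, the difference shrinks.

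**Size: inputs.** From the article: 20 players per group (Section 2.1) and an expected increase (Introduction). Assumed: lognormal markers, their log-SD, the flagging rule and the response pattern. The 0.8 log-SD shift borrows the article's d of 0.8 as a scale; the article does not state it on the log scale.

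**Worked case, log-SD 0.6.** Baseline correlation 0.5; flagged values redrawn by normal-regression imputation on group and baseline; 20 imputations; 1,500 runs.

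Expected raw difference with all data kept:
- All players shift by 0.8 log-SD: exp(0.6²/2) × (exp(0.8 × 0.6) − 1) = 1.197 × 0.616 = 0.737. Simulated: 0.721 and 0.742.
- 20% of the sport group shift by 3 log-SD: 0.2 × 1.197 × (exp(1.8) − 1) = 0.2 × 1.197 × 5.050 = 1.209. Simulated: 1.192 and 1.201.

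After flagged values are replaced:

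| Response | Flagging rule | Flagged of 40 (sport group) | Difference before → after | Share kept |
|---|---|---|---|---|
| All shift 0.8 | 1.5 × IQR fences | 2.09 (1.76) | 0.721 → 0.514 | 71% |
| All shift 0.8 | absolute z above 2 | 2.04 (1.71) | 0.742 → 0.544 | 73% |
| 20% shift 3 | 1.5 × IQR fences | 4.09 (3.59) | 1.192 → 0.082 | 7% |
| 20% shift 3 | absolute z above 2 | 2.14 (2.06) | 1.201 → 0.370 | 31% |

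The sport group holds 1.76/2.09 = 84% to 2.06/2.14 = 96% of the flagged values, which is the condition for shrinkage in the formula above.

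**Sensitivity to the flagging rule, log-SD 0.8.** Flagged values are redrawn from the remaining values of the same group. Share of the mean difference kept:

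| Flagging rule | All shift 0.8 | 20–25% shift 2–3 |
|---|---|---|
| Pooled fence Q3 + 1.5 IQR, raw scale | 56–58% | 1–17% |
| Pooled 3 × IQR fence, raw scale | 73% | – |
| Cut-off of the z above 3 type | 79% | 40–48% |
| Fence within group, raw scale | 81% | 16–42% |
| Pooled fence, log scale | 89% | 28–59% |
| Fence within group, log scale | 95% | 57–83% |

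**Sensitivity to the skew.** With the pooled raw-scale fence and a 0.8 shift, log-SD 0.6, 0.5, 0.4 and 0.3 keep about 69%, 75%, 80% and 85%. With 20% responding by 3 log-SD, the same fence keeps only 4–16% at log-SD 0.3, 0.4 and 0.6. Across the other rules and milder skews examined, the upper ends reach about 99% (all shift) and 90% (20–25% respond).

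In every scenario the share kept was at or below 100%. If observed values are left alone it is 100% by definition.

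**The case against.** The strongest reply is that the sentence is condensed and perhaps loosely worded. It says only that such values will be addressed, not that they will be deleted and redrawn, and the authors may have meant transformation for skewed variables and imputation for missing ones. That is possible, and it limits what can be said about intent. It does not rescue the text: imputation is the only method named for both classes, and an analyst who follows it has to discard real data.

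Three stronger readings are tempting and are not supported:

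- A reader might take the largest losses, to about 56% of the difference or to a few per cent, as the expected damage. Those come from one near-worst-case choice: a fence pooled over both groups on the raw scale, which treats part of the group effect as outlying, with strong skew. Other rules lose much less. The article states neither the rule nor that these markers are right-skewed.
- A reader might infer that both the biomarker hypothesis and the impact–biomarker hypothesis could be rejected because of the rule. The latter is only to be explored and has no rejection criterion; it can be weakened, not rejected.
- A reader might carry the simulated figures over to the planned models. The simulation addresses a raw sport–control mean difference, whereas the model sentence in Section 2.5 speaks of differences between baseline and the testing days. The argument on direction applies wherever flags concentrate in post-match sport-group readings, but that contrast has not been sized.

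Details of the imputation model, the effect measure to report, and sensitivity analyses for injury-related missingness are not part of this error and may properly sit in an analysis plan.

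**Conclusion.** The rule is wrong as written and should be corrected before analysis. This rests on the wording, which is explicit and nowhere qualified, and on the direction of the bias, which is toward no difference whenever high post-match readings are flagged mainly in the sport group.

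The size is not determined by the article. Under assumed lognormal markers with log-SD 0.3 to 0.8 and 20 players per group, the share of the mean difference that survives is roughly 55–99% for a common shift of 0.8 log-SD and roughly 1–90% when 20–25% of the sport group respond strongly. The width of these ranges comes from the unstated flagging rule, the assumed skew and the response pattern. Confidence is high on the error and its direction, and low on any single figure within the ranges.

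**What to change.** In Section 2.5, delete the words *skewed values and*, so that multiple imputation applies to missing values only. State that every observed value is kept unless an assay, sample or recording failure is documented. Handle skewness within the generalized linear mixed models already planned, through a suitable distribution and link, or by log-transforming the biomarkers. The rule covers all data, so the same wording should govern the biomechanical and cognitive-motor outcomes.

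Cost: a change of wording in one section. No extra data, participants or measurements are needed.
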